**Secondary**	
• Assess safety **in pregnant women** randomized to receive the 2-dose Ebola vaccine regimen (Ad26.ZEBOV, MVA-BN-Filo group A) and in control women (unvaccinated pregnant women (group B))	• Frequency and relatedness of all SAEs in women from randomization until study end
• Assess safety **in neonates/infants born** to women randomized to receive the 2-dose Ebola vaccine regimen (Ad26.ZEBOV, MVA-BN-Filo (group A)) and in neonates/infants born to control women (unvaccinated pregnant women (group B))	• Frequency and relatedness of all SAEs in the newborns from birth until study end
• Assess the **reactogenicity** and unsolicited AEs of the 2-dose Ebola vaccine regimen (Ad26.ZEBOV, MVA-BN-Filo) in all vaccinated pregnant women (group A)	• Reactogenicity, defined as local and systemic solicited AEs occurring within 7 days after each dose, and unsolicited AEs within 28 days after each dose: ○ Frequency, grade, duration and causality for solicited systemic AEs and unsolicited AEs ○ Frequency, grade and duration for solicited local AEs
• Describe all pregnancy outcomes	• Pregnancy outcomes (example: normal delivery, Caesarian Section)
• Assess the **immunogenicity** of the 2-dose Ebola vaccine regimen (Ad26.ZEBOV, MVA-BN-Filo) in 150 pregnant women who are anticipated to receive both vaccine doses within the course of their pregnancy (a subset of the 1000 pregnant vaccinated women from group A) compared to 150 non-pregnant women vaccinated after delivery (a subset of group B)	• Anti-EBOV GP binding antibody concentrations, in ELISA units/mL (FANG ELISA) from: ○ Blood samples taken at pre-dose 1, 21 days post-dose 2, at delivery (group A subset only), and 1 year post-dose 1 ○ Cord blood if feasible from women in the group A subset
• Assess **persistence of maternal antibodies** in 75 infants born to women from the group A subset	• Anti-EBOV GP binding antibody concentrations, in ELISA units/mL (FANG ELISA) from a blood sample taken at 14 weeks of age

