^p^In case pregnancy completion/termination in a group A pregnant woman occurs prior to receipt of dose 2, visits 9 and 10 should be performed: visit 10 being relative to visit 9 (2 day window). Visit 5 (dose 2 vaccination with a window of – 14 days, + 28 days) should in this case be performed after visit 9, with visits 6 and 8 being relative to actual dose 2 receipt (visit 5). All of these visits should be captured in RedCap cloud in addition to source documentation. Reactogenicity data (diary completion) should still be performed following dose 2 for group A women that have a pregnancy completion/termination prior to receipt of dose 2

**Table 3 Tab3:** Schedule of activities—women in group B

Visit #	1	2	3	4	5	6	7	8	9^a^	10^n^	11 ^a^	EE
**Visit timing**^**p**^		**Randomiz-ation (D1)**	**D1 + 28 days**	**D1 + 56 days**	**D1 + 12 weeks**	**Pregnancy completion/** **termination**	**Dose 1**	**Dose 2**	**Dose 2 + ** **21 days**	**Dose 2 + ** **28 days**	**Dose 1 + ** **365 days**	**Early** **exit**
**Visit day and window**	**-28 to 1**	**D1**	**D29 ± 7 days**	**D57** ** − 14 days, + 28 days**	**D85 ± 7 days**	**PP 1** ^b^ ** + 2 days**	**PP 43** ^c^ ** + 28 days**	**PP 99** **-14 days, + 28 days**	**PP 120** ** ± 14 days**	**PP 127** ** ± 3 days**	**Dose 1 + 365 ± 28 days**	
**Visit type**	Screening	**Random-ization**	Safety	Safety	Safety	Safety and immuno	**DOSE 1 group B**	**DOSE 2 group B**	Safety and immuno	Safety	Safety and immuno	Early exit
Assessment of understanding	•											
Written informed consent (ICF) ^d^	•											
Inclusion/exclusion criteria	•	•										
Demographics ^**e**^	•											
Medical and obstetric history ^f^ and prestudy meds	•											
Physical examination ^f^	•						•	•				•
Obstetric exam ^f^	•	•				•						•^o^
Targeted physical examination ^f^		•	•	•	•				•	•	•	
Vital signs ^f^ incl. body temperature	•	•	•	•	•	•			•	•	•	•
Urine pregnancy test ^g^	•											
Hematology, chemistry ^g^	•											
Urine dipstick/urinalysis ^g^	•	•	•	•	•							
Syphilis, HIV, hepatitis B and C, malaria screening ^g^	•											
Obstetric ultrasound ^h^	•	•^h^			•							•^o^
Biometric scan		•	•	•	•	•	•	•	•	•	•	•
Contact information	•	•	•	•	•	•	•	•	•	•	•	•
Randomization		•										
Pre-vaccination symptoms^i^												
Vaccination							•	•				
30 min post-vaccination observation ^j^							•	•				
Adverse maternal, fetal outcomes		•	•	•	•	•	•					
SAE recording		•	•	•	•	•	•	•	•	•	•	•

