#### Sample size {14}

The primary outcomes of this unpowered study are adverse maternal, fetal, and neonatal/infant outcomes in vaccinated pregnant women and their neonates. The sample size was determined based on feasibility and estimated background incidence of the primary study outcomes. Background rates for adverse maternal and fetal outcomes in pregnancy are not comprehensively available for Rwanda for all events of interest. However, the Rwanda Demographic Health Survey (2014–2015) [16] provides rates of maternal death (210 per 100,000 live births) and neonatal death (20 per 1000 live births). With the proposed sample size of 1000, the probability of observing at least 1 AE occurring at a rate of 1/1000 is 63%. If no (S)AE (this includes adverse maternal/fetal outcomes) is observed in the vaccine group (*N* = 1000), this would provide 95% confidence that the true incidence is no more than 0.3%.

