## Statistical methods

### Statistical methods for primary and secondary outcomes {20a}

For purposes of analysis, the following populations are defined:Full analysis set (FAS): The FAS will include all randomized participants. All safety analyses will be made on the FASPer-protocol immunogenicity (PPI): The PPI population will include all randomized and vaccinated participants for whom immunogenicity data are available excluding participants with major protocol deviations expecting to impact the immunogenicity outcomes

Of note, women enrolled from Umurinzi will be analyzed separately. No formal statistical testing is planned. The number and percentage of participants screened, enrolled, randomized, receiving two vaccine doses, and completing follow-up will be summarized by study arm.

Baseline demographic characteristics (including gestational age and obstetric risk assessment) will be tabulated overall and by study arm.

The frequency and percentage of women for whom at least one of the indicated adverse outcomes was reported as a primary endpoint (see above) will be summarized by study group. For each separate adverse maternal/fetal and adverse neonatal/infant outcome, the number and percentage of participants who experience at least 1 occurrence of the given event will also be tabulated by study group (groups A and B, and their infants). The verbatim terms used in the CRF by investigators to identify AEs will be coded using the Medical Dictionary for Regulatory Activities (MedDRA). The reporting of the categorical safety data will include the incidence, severity, relatedness, and type of AEs. Continuous safety parameters will be analyzed descriptively (showing the mean, standard deviation, median, and quartiles [Q1 and Q3]).

For participants from group A, all reported AEs, events-related diary information (solicited local at injection site and systemic, and unsolicited) with onset within 4 weeks post dose 1 or dose 2 vaccination (i.e., treatment-emergent AEs) will be included in the analysis. For each AE, the number and percentage of participants who experience at least 1 occurrence of the given event will be summarized. Of note, solicited and unsolicited AEs will not be collected for group B participants.

Summaries, listings, datasets, or participant narratives may be provided, as appropriate, for those participants who die, who discontinue intervention due to an AE, or who experience a severe or a serious AE.

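### Dose-2 adverse-event summaries labelled as vaccinated pregnant women would include group A women given dose 2 after their pregnancy had ended

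*Protocol article*

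**What the plan says.** Dose 2 is scheduled for day 57, with a window of 14 days before to 28 days after (protocol article, Intervention description {11a}). Footnote p to Table 2 covers group A women whose pregnancy ends first. Their dose-2 visit "should in this case be performed after visit 9, with visits 6 and 8 being relative to actual dose 2 receipt (visit 5"), and diary completion "should still be performed following dose 2 for group A women that have a pregnancy completion/termination prior to receipt of dose 2".

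The secondary objective in Table 1 is to assess reactogenicity and unsolicited adverse events "in all vaccinated pregnant women (group A"). Under Statistical methods {20a}, group A events "with onset within 4 weeks post dose 1 or dose 2 vaccination (i.e., treatment-emergent AEs) will be included in the analysis". The safety analysis set does not narrow this: "The FAS will include all randomized participants". The same section promises, by arm, the number and percentage who receive two doses. Section {20b} plans nothing further.

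For immunogenicity, the group A subset consists of 150 women "who are anticipated to receive both vaccine doses within the course of their pregnancy". The analysis set is worded "The PPI population will include all randomized and vaccinated participants for whom immunogenicity data are available", and the sentence goes on to remove women with major protocol deviations expected to affect immunogenicity.

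Sample size {14} states that if no event is seen among the 1000 women of the vaccine group, "this would provide 95% confidence that the true incidence is no more than 0.3" per cent.

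**The concern.** The population named in the objective is not the population that the analysis rule produces. A group A woman who delivers on day 50 and receives dose 2 afterwards has followed the protocol, so she is not a deviation. Her 7-day diary and 28-day unsolicited events are collected, and the analysis rule brings them in. She was not pregnant when she received MVA-BN-Filo, and her unsolicited events fall in the post-partum weeks.

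This matters because of the stated purpose. Objectives {7} says the trial is to describe what follows the two-dose regimen given during pregnancy, in support of relaxing label restrictions. A reader of the dose-2 table needs to know how women who were pregnant at dose 2 fared, and how many there were. A pooled table and a count of two-dose recipients give neither.

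**Working it through.** **1. The plan's own figures.** With n = 1000 and a true rate of 1/1000, P(at least one event) = 1 − 0.999^1000 = 63.2%, which agrees with the stated 63%. The one-sided 95% upper bound with no events is 1 − 0.05^(1/1000) = 0.299%, which agrees with 0.3%. Both reproduce.

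**2. Following one woman through the text.**

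| Step | Place | Result for a woman whose pregnancy ends before dose 2 |
|---|---|---|
| Vaccination | Table 2, footnote p | dose 2 given post-partum |
| Data | Table 2, footnote p | diary still completed |
| Objective | Table 1 | reported under vaccinated pregnant women |
| Analysis rule | {20a} | events within 4 weeks of either dose included |
| Analysis set | {20a} | in the FAS |
| Further splits | {20b} | none planned |

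Dose 1 is always given in pregnancy, so only dose-2 and any-dose summaries are touched.

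**3. How many women?** The documents give no distribution of gestational age at entry, so this is an assumption. Take entry uniform from 13 weeks to a limit U, dose 2 eight weeks later, and delivery at 39.3 weeks. With delivery fixed, the share delivering before dose 2 is (U − 31.3)/(U − 13):

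- U = 32: 0.7/19 = 3.7%
- U = 34: 2.7/21 = 12.9%
- U = 36: 4.7/23 = 20.4%
- U = 38: 6.7/25 = 26.8%

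If delivery varies with an SD of 12 days, the four shares are about 6%, 13%, 20% and 27%.

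A second set of assumptions (entry uniform from 14 weeks to U, delivery at 40 weeks) gives (U − 32)/(U − 14): 2/20 = 10% at U = 34 and 8/26 = 31% at U = 40. Timing within the dose-2 window matters too. At six weeks after dose 1 and U = 34 the share is (34 − 34)/20 = 0%. At twelve weeks and U = 40 it is (40 − 28)/26 = 46%.

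**4. Exposure to dose 2 in pregnancy.** If all 1000 women receive dose 2, shares of 6% and 27% leave about 940 and 730 pregnant at dose 2. The zero-event bounds are 1 − 0.05^(1/940) = 0.32% and 1 − 0.05^(1/730) = 0.41%.

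**5. Effect on a pooled rate.** Pooled rate = (1 − f) × rate in pregnancy + f × rate post-partum, where f is the post-partum share. With purely illustrative rates of 30% and 40%, the pooled figure is 31% at f = 10% and 33% at f = 30%. If the rates were reversed, the shift would go the other way.

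**6. Immunogenicity.** Suppose, as a worst case, that a woman given dose 2 post-partum responds exactly like a group B woman. The observed geometric mean ratio is then the true ratio to the power (1 − f). A true 0.70 would read 0.705 at f = 2%, 0.713 at 5% and 0.725 at 10%.

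**The case against.** The case against has real weight. The SAP is not shown, and a split of a table by pregnancy status is often settled there. Continuing the diaries after a post-partum dose is sound safety practice. Solicited and unsolicited events are not collected in group B, so there is no between-group contrast to dilute. The endpoints are secondary and descriptive. The missing upper gestational-age limit in the listed eligibility criteria is weak evidence: the Discussion describes a restriction on first-trimester recruitment that the list also omits, so the list does not show every gestational-age rule.

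These arguments limit the size and certainty of the point but do not remove it. The article does not merely leave the matter open. It names a pregnant population, provides for non-pregnant vaccinees within it, states an analysis rule that includes them and plans nothing further.

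Three stronger readings are tempting, and the documents do not support them:

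- A reader might infer that post-partum dose-2 women contaminate the immunogenicity comparison. The subset is pre-selected for expected completion in pregnancy, and the PPI set drops major deviations. The article does not say whether a post-partum dose 2 counts as one, and footnote p re-times visits 6 and 8 without mentioning visit 7, the 21-day sample. Retention is possible but not shown.
- A reader might infer that the 0.3% bound is wrong. It is stated for the vaccine group of 1000, all given dose 1 while pregnant, and for that group it is correct.
- A reader might infer that the trial's main results are compromised. The primary maternal/fetal and neonatal/infant outcomes are counted by randomized group and are untouched.

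**Conclusion.** The point holds for dose-2 and any-dose solicited and unsolicited adverse events in group A. As written, these summaries would not describe reactogenicity in pregnancy, and the number of women given MVA-BN-Filo while pregnant would not be reported. The direction of the bias is unknown. The share of about 6% to 27% rests on assumed entry ages, an eight-week interval and full dose-2 uptake; an upper gestational-age limit in the full protocol could make it smaller. Dose-1 results, the primary outcomes and the 0.3% bound for the vaccine group stand. For immunogenicity there is only a residual ambiguity, probably small, and any dilution would be toward no difference. The change is worth making before the tables are fixed, unless the SAP already contains it.

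**What to change.** - Tabulate dose-2 solicited and unsolicited adverse events by pregnancy status at dose 2, with women pregnant at dose 2 as the headline and post-partum recipients beside them. Carry the same distinction into any-dose summaries.
- In the disposition table, split the two-dose count into dose 2 while pregnant and dose 2 after pregnancy ended.
- Keep the 0.3% bound for the vaccine group, and add the zero-event bound for the number actually given dose 2 while pregnant.
- For immunogenicity, state whether a post-partum dose 2 removes a woman from the group A PPI set, and add a sensitivity analysis restricted to subset women pregnant at both doses.

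The cost is analysis wording and a few table columns. The pregnancy-completion and dose-2 visits are already captured, so no new data are needed. The headline dose-2 table will hold somewhat fewer women. No change to dosing or visit rules is proposed.

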### Intervention description {11a}

The Ebola vaccine regimen in this trial is comprised of two vaccines:Ad26.ZEBOV is a replication-incompetent monovalent vaccine encoding the full-length glycoprotein (GP) from Ebola virus (EBOV) Mayinga. A 0.5-mL injection into the deltoid muscle in the upper arm (or thigh if needed) of 5 × 10^10^ vp will be administered at day 1 (enrollment).MVA-mBN226B, further referred to as Modified Vaccinia Ankara (MVA)-BN®-Filo, does not replicate in human cells and is a multivalent vaccine encoding the EBOV GP, the Sudan virus (SUDV) GP, the Marburg virus (MARV) Musoke GP, and the Taï Forest virus (TAFV, formerly known as Côte d’Ivoire ebolavirus) nucleoprotein (NP). A 0.5 mL injection into the deltoid muscle in the upper arm (or thigh if needed) of 1 × 10^8^ InfU will be administered at day 57 (− 14 days + 28 days) after the Ad26.ZEBOV dose.

The second dose of vaccine should ideally be given in the opposite arm/thigh (unless the opposite arm/thigh has a condition that prevents evaluation of the arm/thigh after injection). The Ad26.ZEBOV and MVA-BN-Filo vaccines will be manufactured and provided under the responsibility of Janssen Vaccines and Prevention B.V.

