Humoral immunogenicity sample (serum)							•		•			
Cord blood sample									•		•	
Breast milk sample (*N* = 50)										•		

pre-dose;

pre- and post-dose

^a^Visits 7 and 11 for group A immunology subset participants only

^b^PP 1 refers to the day of pregnancy completion/termination. Visit 9 (PP 1) should occur on the day of pregnancy completion/termination or within 2 days

^c^Visit 10 (PP 43) scheduled to occur at routine 6 week post-partum visit. For women from group A not part of the immunogenicity subset, this visit will be the end of the trial

^d^Must be signed before first study-related activity

^e^Maternal demographic information to be collected at screening includes date of birth, race/ethnicity, education level, geographical location/residence, occupation, household size (number of persons living in the same home), and international travel history

^f^Information to be collected for medical and obstetric history, physical exams, and vital signs is specified in the protocol

^g^Urine dipstick for protein and glucose will be performed at these visits. If results 1 + or greater, then additional work-up for pre-eclampsia or gestational diabetes may be warranted

^h^Ultrasound not required at visit 2 if screening (visit 1) ultrasound completed within past 10 days and no other indication for ultrasound

^i^Investigator must check for acute illness or body temperature ≥ 38.0 °C at the time of vaccination. In such cases, the participant may be vaccinated at later time point

^j^Participants will be closely observed for a minimum of 30 min post-vaccination

^k^In all women of group A, solicited AEs (reactogenicity) and unsolicited AEs will be assessed 7 days post each dose and 28 post each dose respectively

^l^Includes any medical treatment/medications given to the mother during delivery (e.g., antibiotic prophylaxis)-specifying names of medications administered

^m^Information to be collected for delivery history and post-pregnancy examination is specified in the protocol

^n^Any routine laboratory assessment performed at time of delivery and other laboratory tests as medically indicated

^o^Not required if participant is not pregnant

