Concomitant medications ^k^	•	•	•	•	•	•	•	•	•	•	•	•
Delivery history ^l^						•						
Post pregnancy physical examination ^l^						•						
Laboratory assessments ^m^						•						
Group B immunology subset supplemental procedures (*N* = 150)	**1**	**2**	**3**	**4**	**5**	**6**	**7**	**8**	**9**	**10**	**11**	EE
Humoral immunogenicity sample (serum)									•		•	
Breast milk sample (*N* = 10)												

pre-dose;

pre- and post-dose

^a^Visits 9 and 11 for group B immunology subset participants only

^b^PP1 refers to the day of pregnancy completion/termination. Visit 6 (PP1) should occur on the day of pregnancy completion/termination or within 2 days

^c^Visit 7 (PP 43) scheduled to occur at routine 6 week post-partum visit

^d^Must be signed before first study-related activity

^e^Maternal demographic information to be collected at screening includes: date of birth, race/ethnicity, education level, geographical location/residence, occupation, household size (number of persons living in the same home), and international travel history

^f^Information to be collected for medical and obstetric history, physical exams, and vital signs is specified in the protocol

^g^Urine dipstick for protein and glucose results will be performed at these visits. If results are 1 + or greater, then additional work-up for pre-eclampsia or gestational diabetes may be warranted

^h^Ultrasound not required at visit 2 if screening (visit 1) ultrasound completed within past 10 days and no other indication for ultrasound

^i^Investigator must check for acute illness or body temperature ≥ 38.0 °C at the time of vaccination. In such cases, the participant may be vaccinated at later time point

^j^Participants will be closely observed for a minimum of 30 min post-vaccination

^k^Includes any medical treatment/medications given to the mother during delivery (e.g., antibiotic prophylaxis)-specifying names of medications administered

^l^Information to be collected for delivery history and post-pregnancy examination is specified in the protocol

^m^Any routine laboratory assessment performed at time of delivery and other laboratory tests as medically indicated

^n^Visit 10: for women not part of the immunogenicity subset this visit will be the end of the trial

^o^Not required if participant is not pregnant

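### The schedule tables contradict themselves on follow-up after dose 2, and footnotes c and n can end the trial before that follow-up is complete

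*Protocol article*

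**What the plan says.** Tables 2 and 3 (Participant timeline {13}) have two header rows for each visit. One gives the timing in words, such as dose 2 plus 28 days. The other gives a study day with a window, counted from D1 in group A and from pregnancy completion (PP 1) for the post-delivery visits.

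- **Dose 2.** Under Intervention description {11a}, the second vaccine "will be administered at day 57 (− 14 days + 28 days) after the Ad26.ZEBOV dose". Table 3 prints the group B dose 2 visit as "PP 99 -14 days, + 28 days".
- **Group B, visit 10.** It is timed at dose 2 plus 28 days, with printed window PP 127 ± 3. Footnote n: "Visit 10: for women not part of the immunogenicity subset this visit will be the end of the trial".
- **Group A, visits 6 and 8.** They are timed at dose 2 plus 7 and plus 28 days, with printed windows D64 ± 3 and D85 ± 7.
- **Group A, visit 10.** Printed window PP 43 ± 14. Footnote c: "For women from group A not part of the immunogenicity subset, this visit will be the end of the trial".
- **Group A, delivery before dose 2.** Footnote p keeps dose 2 after visit 9, "with visits 6 and 8 being relative to actual dose 2 receipt (visit 5". Visit 10 stays tied to visit 9, that is, to delivery.
- **Safety periods.** Table 1 asks in group A for "unsolicited AEs within 28 days after each dose" and, in women of both groups, for SAEs from randomization to study end. Table 2 footnote k says that in group A "solicited AEs (reactogenicity) and unsolicited AEs will be assessed 7 days post each dose and 28 post each dose respectively".

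**The concern.** The printed days are correct only for a dose 2 given on its nominal day. Footnote p is the only text that ties visits to the actual second dose. It covers visits 6 and 8 in one situation, in Table 2 only, and Table 3 has no counterpart. Nothing says which header row prevails.

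A site that schedules by the day row, or closes participation by footnotes c and n, could do three things after a late dose 2 or an early delivery:

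- stop SAE recording in a non-subset group B woman within days of her second dose;
- hold the last unsolicited adverse event visit of a group A woman well short of 28 days;
- discharge a non-subset group A woman who delivered early before her remaining visits, or even before dose 2.

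The endpoints at stake are secondary, but this is a safety study meant to support a label change. Events missed through shortened follow-up make the observed rates too low.

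**Working it through.** **Nominal days.** Group A: 57 + 7 = D64 and 57 + 28 = D85. Group B: 43 + 56 = PP 99 and 99 + 28 = PP 127. All the printed days reproduce, so they are offsets from the nominal dose 2 day.

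**Group B, visit 10 (Table 3).**
- Dose 2: 99 − 14 = PP 85 to 99 + 28 = PP 127, which is 43 permitted days.
- Visit 10: PP 124 to PP 130.
- Dose 2 plus exactly 28 days falls inside the printed window only for dose 2 at PP 96–102 (7 of 43 days).
- Allowing the 3-day tolerance (28 − 3 = 25 days), the latest workable dose 2 is 130 − 25 = PP 105. For PP 106–127 (22 of 43 days) the two rows cannot both be met.
- With dose 2 at PP 127, visit 10 falls between 124 − 127 = −3 and 130 − 127 = +3 days from the dose.
- This needs no unusual interval between doses. Dose 1 is allowed up to 43 + 28 = PP 71, and the nominal 56 days then gives 71 + 56 = PP 127.

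**Group A, dose 2 during pregnancy (Table 2).**
- Dose 2: D43 to D85, again 43 days. Visit 6: D61–67. Visit 8: D78–92.
- Dose 2 plus exactly 28 days falls inside the visit 8 window for dose 2 at D50–64 (15 of 43 days).
- Allowing the 7-day tolerance (28 − 7 = 21 days), the latest workable dose 2 is 92 − 21 = D71. For D72–85 (14 of 43 days) the rows cannot both be met.
- With dose 2 at D85, the visit 6 window closed 85 − 67 = 18 days before the dose, and the visit 8 window closes 92 − 85 = 7 days after it. Visit 8 is the last visit at which Table 2 marks unsolicited event collection.
- SAE recording runs on to visit 10, no earlier than PP 43 − 14 = PP 29. A dose given by the day of delivery (PP 1) therefore has at least 29 − 1 = 28 days of SAE follow-up.

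**Group A, delivery before dose 2, outside the subset.** Let delivery be on study day T. Nominal visit 10 (PP 43) is then day T + 42.
- It precedes nominal visit 8 (D85) if T + 42 < 85, that is, delivery before D43.
- It precedes nominal dose 2 (D57) if T + 42 < 57, that is, delivery before D15.
- Example with windows: delivery on D8 and dose 2 on D57 puts dose 2 at 57 − 8 + 1 = PP 50. Visit 10 at PP 29–57 falls from 21 days before to 7 days after that dose, while 28 days after dose 2 is PP 78.

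**The case against.** The strongest reply is that the timing row already defines these visits by dose 2, and that the D and PP numbers are plainly nominal. Section {11a} supports this. Taken literally, Table 3 would permit dose 1 at PP 71 and dose 2 at PP 85, only 14 days apart, which {11a} excludes. The group A adverse event period is also fixed by dose in Table 1, in footnote k and in Statistical methods {20a}, which analyses events with onset within 4 weeks of either dose. Footnote p, as the specific rule, should override footnote c. And the article condenses a full protocol that is not shown.

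Much of this stands, and it rules out several stronger readings that a reader might infer:

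- **That the visits are not tied to dose 2 at all.** The timing row ties them, so the defect is a conflict between two rows.
- **That SAE follow-up is cut throughout group A.** It is not for women dosed before delivery, and subset women continue to dose 1 plus 365 days.
- **That group B loses a planned 28-day adverse event period.** {20a} says that solicited and unsolicited events are not collected there. Only SAE follow-up of non-subset women can shorten.
- **That about half of group B is affected.** The 22 of 43 and 14 of 43 are calendar days, not women, and the document gives no distribution of dose 2 timing.

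The reply does not dispose of the point. Footnote p shows that an express rule was thought necessary, yet it is limited to one situation in one table. Nothing ranks the two header rows. Footnotes c and p conflict whichever row governs. These are contradictions in printed text, not detail left to the full protocol.

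**Conclusion.** The point holds as an internal contradiction in the schedule tables, in three parts.

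1. **Group B, outside the subset.** If the printed window governs, SAE follow-up after the latest permitted dose 2 ends within 3 days of that dose.
2. **Group A, late dose 2 in pregnancy.** The printed windows conflict with the 28-day unsolicited event period. For dose 2 at D85, the visit 8 window closes 7 days after the dose. SAE follow-up is not cut.
3. **Group A, outside the subset, delivery before dose 2.** Footnote c can end the trial before visits, or a dose, that footnote p requires.

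Parts 1 and 2 depend on a site following the day row; part 3 does not. The number of women affected cannot be derived from the document. The primary endpoints, which run to 6 weeks after pregnancy and to 14 weeks of infant age, do not depend on these visits. The change is worth making because it is cheap and protects planned safety follow-up, but it is no threat to the main results.

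**What to change.** State in Tables 2 and 3 that all post-dose-2 visits are counted from the actual date of dose 2, with their existing tolerances. The D and PP numbers may stay if marked as nominal. One general note extending the rule in footnote p would do. It should also cover the 21-day visits (visit 7 in Table 2, visit 9 in Table 3), which have the same double header.

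Reword footnotes c and n so that end of trial outside the subset is the later of the stated visit and the 28-day post-dose-2 visit, and reconcile c with p.

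For every permitted dose 2 day, the 28-day visit then falls 25 to 31 days after the dose in group B (28 ± 3) and 21 to 35 days after it in group A (28 ± 7). The dosing windows are not touched.

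The cost is a change to table notes and two footnotes. Some women stay in follow-up a few weeks longer, with no added visits.
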